### Analysis populations

All analyses and data summaries will be conducted on the intention-to-treat (ITT) population which is defined as all participants registered regardless of non-compliance with the protocol or withdrawal from the study.

### Statistical analysis

#### Baseline characteristics

Data from the baseline socio-demographic, computer usage and clinical data questionnaires will be tabulated using frequencies and summary statistics for each treatment group and overall for both the pilot phase and full trial.

### Primary outcome

The FACT-G Physical Well-being score will be summarised overall and by treatment arm. Changes in score over time and differences between treatment arms will be explored using a multilevel repeated measures model. The model for each post-randomisation point will be adjusted for baseline score and stratification factors. If there are missing items, subscale scores will be prorated as per the FACT-G scoring manual.

### Secondary outcomes

#### Clinical process measures

The number of calls made to the hospital will be summarised overall and by treatment arm. Differences between the two treatment groups will be compared using either Poisson regression or negative binomial regression; the most appropriate model will be chosen after performing post-estimation tests. Models will be adjusted for the stratification factors.

The numbers of weekly/additional AE reports and severe AE alerts generated will be summarised for participants randomised to the eRAPID intervention. The number of telephone calls to hospital staff, acute admissions, contacts with GP and/or community services and number of deaths will be summarised overall and by treatment arm. Any differences between treatment arms will be explored using the most appropriate regression model (either Poisson or negative binomial, to be decided using post-estimation tests) adjusted for stratification factors.

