## Background

Systemic drug treatments for cancer (chemotherapy, hormonotherapy, biological therapy, targeted agents) are associated with significant adverse events (AEs). An AE is an untoward symptom or disease associated with (but not necessarily causally related to) a medical treatment or intervention AEs may lead to changes in drug dosage, cessation of treatment and can significantly compromise patients’ quality of life. Severe AEs can escalate to hospitalisation for potentially life-threatening toxicities: 18% of cancer patients present to emergency services within 14 days of a scheduled hospital visit for symptom management (infection, fever, nausea/vomiting, pain, breathlessness) [1–4]. Patients with breast, gastrointestinal, colorectal cancers and those with metastatic disease are amongst those most likely to have emergency admissions [4, 5].

Many patients however, delay seeking care especially out of hours [3, 5]. This concurs with the findings of a UK enquiry into patient outcome and death (National Confidential Enquiry into Patient Outcome and Death, NCEPOD) which found that of patients dying within 30 days of systemic cancer therapy, 17% delayed seeking advice for over 24 h [6]. AEs are documented consistently by physicians in clinical trials however in routine care recording of AEs by clinicians and reporting by patients is variable and often omitted [6]. It has been recognised for some time that a structured AEs reporting system would be useful to facilitate correct documentation and grading of AE severity to support tailored management. Consequently, the National Cancer Institute (NCI) in the US have developed the Common Terminology Criteria for Adverse Events (CTCAE v 4.0) [7] as a reporting and severity grading system for cancer clinical trials. These have recently been adapted for patients to self-report (NCI-PRO CTCAE) [8] and these items have concordance with nurse evaluated AE [9] and similar items created for self-report correlate with quality of life measures [10]. The need for routine monitoring of cancer treatment AE is at odds with a health care system relying increasingly on patient self-management and home based care. In order to bridge the gap in service provision to detect, identify and manage AE in cancer patients the Electronic patient self-Reporting of Adverse-events: Patient Information and aDvice (eRAPID): system was developed [11].

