### Randomisation

After trial eligibility has been confirmed and consent given, randomisation is performed via the University of Leeds Clinical Trials Research Unit (CTRU) telephone system. Participants are randomised with 1:1 allocation to intervention and control groups. Patients are stratified by cancer site (breast, gynaecological or colorectal), gender and previous chemotherapy (gynaecological cancer patients only) in variable random permuted blocks of 4, 6 or 8, see Fig. 4.

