13-item scale for measuring the level of patient engagement in their healthcare (knowledge, skill and confidence for self-management)	Statements rated on 4 point scale from disagree strongly to agree strongly and additional N/A option.	• When all is said and done I am the person who is responsible for taking care of my health	Baseline, 18 weeks and 12 months
		• I am confident I follow through on medical treatments I may need to do at home	
	Responses are combined to provide a single score of between 0 and 100 with higher scores representing higher levels of patient activation.	• I know what treatments are available for my health problems.	
	Scores can be classified into one of four groups, known as ‘levels of activation’.		
Secondary outcomes- eRAPID/IT system performance			
System Usability Scale (SUS) [42]			
10 item instrument to assess views of usability of an IT systems.	Each statement rated from 1 strongly disagree to 5 strongly agree.	• I think that I would like to use this system frequently	18 weeks
		• I thought there was too much inconsistency in this system	
	Responses are calculated into a total score ranging from 0 to 100 with higher scores representing better system usability.	• I felt very confident using the system	
eRAPID end of study questionnaire			
15 statements/free text boxes to assess participant views of using eRAPID and suggestions for improvements	Statements rated on 3–5 response option scales (e.g. very easy-very difficult) and free text boxes for comments.	• How easy or difficult was it to learn how to use the eRAPID system?	18 weeks
		• How did you feel about the amount of time it took to complete the symptom questions?	
		• To what extent do you feel that the symptom questionnaire was useful for the doctors and nurses you saw during your treatment?	
		• Have you got any suggestions about how the eRAPID system could be improved?

**Table 2 Tab2:** eRAPID RCT in systemic cancer treatment: Researcher collected data for secondary outcomes

Data	Description of data	Time point for collection
Treatment and clinical information	• Cancer diagnosis, stage and grade	Initial baseline assessment and reviewed for changes at 18 weeks
	• Age, date of birth	
	• Baseline data on planned chemotherapy	
	• Changes to treatment delivery and reason	
	• Comorbidities	
Clinical process- Hospital contacts	• Contacts with the hospital e.g. (unplanned) telephone, appointments, consultations	• Data extracted from medical notes for 18 of study

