#### Patient outcome measures (other than primary)

Changes in scores over time and differences between treatment arms will be explored using a multilevel repeated measures model adjusted for baseline scores and stratification factors. As the sample size was not powered to detect changes in these outcome measures, statistical significance will be assessed at the 1% level.

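### The process-measure models adjust for stratification factors only and leave out baseline metastatic status, which is collected and which the Background links to emergency admission; the analysis stays valid, but some precision and robustness is given up

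*Protocol article*

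**What the plan says.** The Background of the protocol article, describing who presents with severe adverse events, says that "those with metastatic disease are amongst those most likely to have emergency admissions". Breast and gastrointestinal or colorectal cancers are named in the same sentence.

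Table 2 (Outcome measures) lists "Cancer diagnosis, stage and grade" among the items recorded at the initial baseline assessment and reviewed for changes at 18 weeks.

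The Randomisation section reads "Patients are stratified by cancer site (breast, gynaecological or colorectal), gender and previous chemotherapy (gynaecological cancer patients only"). Stage is not listed.

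Under Inclusion criteria, breast patients must be on a neo-adjuvant or adjuvant pathway. Gynaecological and colorectal patients need only require chemotherapy, with no restriction on stage.

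Under Clinical process measures, the model for calls is followed by "Models will be adjusted for the stratification factors". The next paragraph gives the same rule for acute admissions, GP and community contacts, and deaths. The questionnaire outcomes get one covariate more. For the primary outcome, "The model for each post-randomisation point will be adjusted for baseline score and stratification factors", and the other patient-reported scores are treated alike.

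**The concern.** The process measures have the thinnest adjustment in the plan. The questionnaire models carry the baseline score, which absorbs much of what separates patients at entry; the count models name nothing beyond the strata. Yet the one prognostic statement in the document that concerns a process measure is about metastatic disease and emergency admission. Stage is recorded, can vary within two of the three cancer sites, and is neither balanced by design nor adjusted for.

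Two things follow. Variation in counts that stage could explain stays in the residual. And if the arms differ in metastatic share, the baseline table will show it and no planned analysis will address it; adding stage after seeing the imbalance would carry little weight. Acute admissions are also a safety measure under Aims and study objectives, and health-care use feeds the cost-effectiveness analysis, which that section calls the main secondary outcome.

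**Working it through.** **Inputs from the document.** 252 per arm (504 in total), 1:1 allocation, stratification by site. The size reproduces: 2 × (1.96 + 0.842)² × 6.7² / 2² = 176.2, against the stated 176 per arm; power at 176 is 80.0%; 176 / 0.7 = 251.4, rounded up to 252.

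**Assumptions.** The document gives no site mix, metastatic share or stage effect. Taken here: half of patients non-breast; half of those metastatic, so 25% overall; no metastatic breast patients, given the eligibility rule; stage rate ratio 1.5 to 3.

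**Chance imbalance.** With 126 non-breast patients per arm:
- SD of the between-arm difference among non-breast patients: √(2 × 0.5 × 0.5 / 126) = 0.063.
- Over the whole sample: 0.5 × 0.063 = 0.0315.
- 95% range: 1.96 × 0.0315 = 0.062, about 6 points overall; 1.96 × 0.063 = 0.123, about 12 points among non-breast patients.

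**Shift in the crude rate ratio with no true effect.** A 6.2-point difference around 25% means 28.1% against 21.9%. Shift = (1 + (RR − 1) × 0.281) / (1 + (RR − 1) × 0.219):

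| Stage rate ratio | Calculation | Shift |
|---|---|---|
| 1.5 | 1.1405 / 1.1095 | about 3% |
| 2 | 1.281 / 1.219 | about 5% |
| 3 | 1.562 / 1.438 | about 9% |

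Adjusting for site does not remove this. Stratification already makes site nearly equal between arms, so the site-adjusted Poisson estimate is close to the crude one.

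**Sensitivity.** With a non-breast share of 40% to 60% and 30% to 50% of those metastatic, the overall SD is 2.6 to 3.5 points and the 95% range 5 to 7 points. At a stage rate ratio of 3 the shift is (1 + 2 × 0.1453) / (1 + 2 × 0.0947) = 1.085 at the low end and (1 + 2 × 0.3338) / (1 + 2 × 0.2662) = 1.088 at the high end, so it hardly depends on these shares.

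**Precision.** Negative binomial counts were simulated with N = 504, allocation stratified by breast/non-breast, the shares above, dispersion 1, baseline mean 0.5 or 2, and a treatment rate ratio of 0.75 (400 trials per setting). The model with site was compared with the model with site and stage:

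| Stage rate ratio | Reduction in variance of log rate ratio |
|---|---|
| 1.25 | 0.1% to 0.3% |
| 1.5 | 0.6% to 1.2% |
| 2 | 2.4% to 4.1% |
| 3 | 6.7% to 10.2% |

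Simulated power changed by between −0.5 and +2.5 points.

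**Validity.** With no treatment effect (baseline mean 0.5, 800 trials per setting), the model without stage rejected in 5.9%, 5.1% and 4.4% of trials at stage rate ratios of 1.5, 2 and 3. The simulation error is √(0.05 × 0.95 / 800) = 0.8 points, so this is consistent with 5%.

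**Physical Wellbeing, for comparison.** With residual SD 6.7 × √(1 − R²), power at 176 per arm rises from 80.0% to 80.4%, 80.7%, 81.9% or 83.9% if stage explains a further 1%, 2%, 5% or 10% of variance.

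**The case against.** The strongest defence is that adjusting for stratification factors is a standard, valid choice, and that an unseen analysis plan could add covariates. Validity stands. On the second part, the article is not silent: it states a covariate rule for these outcomes, and that rule omits stage. What can be said is that the rule could be better, not that it is wrong.

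Several stronger readings are tempting and are not supported:

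- **That precision and protection are lost, or the result biased.** Site stratification already separates a breast cohort treated without metastatic intent, and gynaecological patients are further split by previous chemotherapy. The shift above sits at the edge of the chance range and is covered by the confidence interval.
- **That an imbalance of 8 to 9 points is to be expected within the 95% range.** 1.96 × √(2p(1 − p) / 252) gives 8.0 to 8.7 points for p of 0.3 to 0.5, but this treats the sample as unstratified. If half are breast patients, 50% metastatic overall would mean every non-breast patient is metastatic, and stratifying by site would then balance stage.
- **That the document calls metastatic disease a driver of all the outcomes.** It reports a cited association, without a rate, for emergency admissions only. Extending it to calls and contacts is a reasonable expectation, not a statement in the text.
- **That age should be added, or that the coding of the strata is faulty.** No passage calls age prognostic, and coding is detail for the analysis plan.
- **That no process measure has a baseline value.** The Health-economic data section says community and outpatient care use is collected at baseline, while Table 1 lists the resource-use form from 6 weeks only. The count models name no baseline value either way.

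**Conclusion.** The point holds as a modest, nearly free improvement. The process-measure models omit a recorded baseline variable that the document itself links to emergency admission, and which can vary among colorectal and gynaecological patients. The cost is some precision and some robustness to chance imbalance: about 6 points of possible imbalance overall, a crude rate-ratio shift of about 3% to 9%, and about 1% to 10% of the variance of the log rate ratio for stage rate ratios of 1.5 to 3. The upper ends need a ratio of 3; at 1.5 to 2 the variance gain is about 1% to 4%. These figures rest on the assumed site mix, metastatic share and stage effect. The case is strongest for acute admissions.

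**What to change.** Under Clinical process measures, pre-specify metastatic status at baseline (yes/no) as a fixed covariate, alongside the stratification factors, in the models for acute admissions, calls, and GP and community contacts. Use it also in the cost analysis if that is regression-adjusted; the article states no covariates there. Derive it from the stage recorded at the initial assessment, not from the 18-week review, which follows randomisation.

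The cost is one or two model degrees of freedom and a stated rule for missing stage. No new data are needed, and in a log-link count model without a treatment-by-stage interaction the treatment rate ratio stays essentially the same target. The wording should be settled before outcomes are compared by arm. Adding stage to the Physical Wellbeing model is optional, since little gain is expected beyond the baseline score.

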#### Patient outcome measures (other than primary)

Changes in scores over time and differences between treatment arms will be explored using a multilevel repeated measures model adjusted for baseline scores and stratification factors. As the sample size was not powered to detect changes in these outcome measures, statistical significance will be assessed at the 1% level.

### Health-economic data

An embedded health-economic study will allow within trial incremental cost-effectiveness analysis (18 weeks) taking the perspective of the service provider including the costs of NHS and Personal Social Services. The analysis will compare usual care with the eRAPID-supported pathway. A secondary analysis will take a societal perspective. Analyses will use quality-adjusted-life-years (QALYs) outcome-measures. Estimation of QALYs requires the production of utility-weights for each health-state observed in the trial population. We will use the EQ-5D-5 L for this purpose [3, 44] collected at baseline, 6, 12 & 18 weeks. We will also use EORTC QLQ-C30 to derive utilities (EORTC QLQ-U10) to calculate QALYs in the same way. This will limit the need to interpolate quality of life between observation points [45]. NHS resource-use associated with each treatment modality will be collected using the process-of-care measures to contribute to a health-economics analysis of additional health financial costs related to treatment and the study. Use of outpatient and community-based health and social care (including, for example, home help or residential care) will be collected from the patient at baseline, 6, 12, and 18 weeks with the Use of Resources questionnaire developed in the Programme Development Grant and tested in the pilot study. Unit financial costs for health services resources will be obtained from national source: the Personal Social Services Research Unit, the British National Formulary and NHS reference cost database [46–48]. Given the duration of the trial discounting is not required.

Secondary analysis will include costs to participants (travel expenses, over the counter medicines) and productivity losses.

In addition to the analyses at 18 weeks we will undertake an exploratory cost effectiveness analysis (including a planned a–priori sub-group cost-effectiveness analysis at 12 months using a sub-sample of participants for whom we have collected resource use, EQ-5D-5 L and EORTC QLQ-C30 data).

For each analysis we will undertake probabilistic sensitivity analysis using bootstrapping. The results will be presented as the Expected Incremental Cost Effectiveness Ratio, scatter plot on the cost-effectiveness plane and a Cost Effectiveness Acceptability Curve. We will calculate the expected net-benefit assuming lambda has a value of £20,000 [49].

### Qualitative data

Interviews will be recorded and transcribed. Data will be managed by NVivo software and analysed using thematic analysis [37, 50]. Two researchers will independently look for the emerging themes and code them. Then they will meet, compare the codes/themes and resolve any potential conflicts by consensus.

## Discussion

This paper describes the protocol for the eRAPID RCT in systemic cancer treatment. eRAPID is a unique web based intervention designed to improve the systematic reporting of AE during cancer treatment and improve patient care and experiences. A number of web based PROMs systems have been developed. Since the current trial began Basch and colleagues in the U.S. have published findings from an RCT using the STAR (Symptom Tracking and Reporting) web interface during chemotherapy indicating a positive impact on patients’ quality of life, treatment delivery, number of emergency room attendances and 1 year survival [44]. We believe eRAPID is the first of its kind to allow remote monitoring of symptoms and side effects where patient reported data is accessible alongside standard clinical information in electronic patient records as well as providing patients with immediate symptom management advice. We hypothesise that these features along with alerts for severe symptoms will lead to improved clinical outcomes for participants allocated to the eRAPID intervention and will benefit health care services.

This study can be considered a complex intervention due to the number of active components involved. These include the new technology for patients completing symptom self-reports from home, automatic advice on managing mild symptoms and when to contact the hospital for severe problems, the availability of this patient data for staff to use in clinical practice, alert generation for severe problems and maintaining staff training and engagement. Consequently eRAPID’s success relies on the investment of both staff and patient groups in the intervention and the robustness of the IT supporting the system. Although the eRAPID website and the online symptom reporting questionnaire have undergone extensive usability testing, the pilot phase of the RCT was considered vital in order to assess the intervention over a longer time frame and with all participating cancer groups as each differ in terms of the care pathways and staff involved. The decision to perform an internal pilot, rather than a separate pilot study, was motivated by our intention to avoid losing momentum and reduce the time between the end of the pilot and the start of the main trial [45]. This approach aimed to maintain continuity with the staff involved in the eRAPID intervention both in terms of recruitment and utilising the patient AE reports in clinical encounters.

The study is funded as part of 5 year programme, in parallel we are developing multi-centre eRAPID interventions for cancer patients receiving radiotherapy and surgery which will be evaluated in separate pilot studies. If found to have a positive effect on patient wellbeing and use of health care resources, eRAPID has the potential to provide a cost effective enhancement to the standard care of cancer patients. Such an approach could also be extended to long-term survivorship beyond cancer treatment [49].
